### Data collection and management

All data will be collected at baseline, 12 and 24 months. CVD hospitalisations and cardiovascular events will be collected via state-based administrative admissions data (depending on location of recruited practices). Individual patient deaths will be collected via linkage with the National Death Index and medication prescriptions and health service utilisation via linkage with the Australian Government Department of Health Pharmaceutical Benefits Scheme (PBS) and Medical Benefits Scheme (MBS) schemes respectively. Probabilistic matching will be used to link records and the estimated proportion of invalid and missed links using data linkage will be very low [26]. Data collection pertaining to the proportion of patients with chronic disease management plans and achieving national risk factor targets (cholesterol, smoking, and BP) will be electronically extracted from participating practice software systems using an automated data extraction tool with encrypted identifiers attached to patient data.

All data will be stored on a password-protected Secure Unified Research Environment (SURE), which is a purpose-built, remote-access data storage facility. This environment allows researchers to safely access, store and analyse study data [27]. Only aggregated and analysed data can be exported and data in SURE cannot be copied, downloaded or transmitted by email or other means. Only trained study research staff will have access to the SURE facility through a staff-specific username and password. The linked dataset will therefore be anonymised and the research team who will be analysing the data and delivering the intervention will not have access to individual-level data. This maximises privacy and forms an important aspect of the requirements for waiver of consent approval. Electronic files containing linked data for analysis will be stored on a Virtual Project Workspace within SURE and the access period shall be from study commencement for 7 years to enable all analyses to be completed. At the end of this data retention period, the tapes holding the archived data files will be physically destroyed.

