### Intervention and control groups

Practices allocated to the intervention will participate in a CHD secondary prevention collaborative quality improvement program. The program is designed to use data and practice level engagement to implement rapid and progressive changes based on Plan, Do, Study, Act (PDSA) cycles for pre-determined performance targets [21]. The program is underpinned by the psychology of behaviour change, active practice-level engagement combined with extraction and utilisation of electronically extracted data from practice software [12]. Practices will collaborate and support each other between and within practices in an ongoing way over 12 months to achieve a set of key performance measures (Table 1). These measures have been pre-determined based on guidelines [6] and availability of data for extraction and were developed and approved through an iterative process involving study investigators, clinicians and quality improvement experts. Intervention practices will receive their summarised performance data monthly.

**Table 1 Tab1:** QUEL intervention key performance measures

• Proportion of patients with CHD where LDL has been recorded within the previous 12 months	
• Proportion of patients with CHD whose most recent LDL result was less than 2.0 mmol/L	
• Proportion of patients with CHD with a recorded BP reading taken within the previous 12 months	
• Proportion of patients with CHD whose most recent BP reading, taken within the previous 12 months, was less than or equal to 130/80 mmHg	
• Proportion of patients with CHD whose smoking status has been recorded	
• Proportion of patients with CHD recorded as a current smoker	
• Proportion of patients with CHD who are currently prescribed an anti-platelet agent	
• Proportion of patients with CHD who are currently prescribed a statin	
• Proportion of patients with CHD who are currently prescribed an ACE inhibitor or ARB	
• The proportion of patients with CHD with MBS Items 721 or 732 claimed (GP Management Plans or review)	
• Proportion of patients with CHD who have an influenza vaccination recorded within the previous 12 months	

*CHD* Coronary heart disease, *LDL* Low density lipoprotein, *BP* Blood pressure, Angiotensin-converting-enzyme (ACE) inhibitor, *ARB* Angiotensin II receptor blockers, *MBS* Medicare Benefits Scheme, *GP* General practice

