### Outcomes

The primary outcome is the proportion of patients with unplanned CVD hospitalisations within 2 years of baseline data extraction (and commencement of intervention for those allocated to intervention group). For this study, CVD is defined as any condition involving the heart, brain or peripheral blood vessels and includes CHD (such as angina and myocardial infarction, MI), cerebrovascular disease (such as stroke), peripheral arterial disease and other conditions including heart failure and atrial fibrillation [25].

Secondary outcomes, also at 2 years) are;
i.Proportion of patients with major adverse cardiac and cerebrovascular events (fatal and non-fatal) that includes CHD (angina or MI), stroke or CVD death,ii.proportion of patients who received guideline-recommended medicines,iii.proportion of patients with a chronic disease management plan or review (Australian Medicare Item numbers 721 or 732 respectively) and;iv.proportion of patients achieving national targets for CVD risk factors (total cholesterol, systolic blood pressure, smoking).

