### Statistical analyses

Analyses will be conducted at the individual level while accounting for clustering of patients within practices. Intention-to-treat principle will be followed with patients analysed according to their randomisation group. Differences in the proportion of patients who are hospitalised (as well as binary secondary outcomes) will be analysed using log-binomial regression or robust Poisson regression in case of convergence issues. Clustering will be accounted for by modelling the correlation among patients from the same cluster using generalised estimating equations with an exchangeable correlation structure. Sensitivity analyses will include analyses of yearly rates using Poisson regression and/or time-to-event analyses via Cox models. Adjusted analyses will also be performed to account for baseline imbalances in cluster and patient characteristics. Pre-specified sub-group analyses will be used to determine the impact of the intervention on different patient groups (male v female; low SES v high SES, different CVD subgroups, influenza vaccination or not) and practice types (e.g., large v small and urban v rural). This will be done by adding the subgroup variable as well as its interaction with the intervention to the main analysis model. As data will be extracted from primary care practice clinical records and administrative data, if not recorded, it will be assumed that the task has not been done. A detailed analysis plan including mock tables will be developed and signed-off prior to unblinding.

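### The care-plan outcome is defined by Medicare items 721/732 but is read from unblinded practices' own software rather than from the MBS claims already to be linked, so better recording could count as more plans

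*Protocol article*

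**What the plan says.** All references are to the protocol article.

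- **Definition.** Outcomes lists, as the third secondary outcome at 2 years, the "proportion of patients with a chronic disease management plan or review (Australian Medicare Item numbers 721 or 732 respectively").
- **Linked source.** Data collection and management obtains "health service utilisation via linkage with the Australian Government Department of Health Pharmaceutical Benefits Scheme (PBS) and Medical Benefits Scheme (MBS) schemes respectively".
- **Source assigned to this outcome.** Later in the same paragraph, "Data collection pertaining to the proportion of patients with chronic disease management plans" is grouped with that on the three risk factors, and the article says that all of it "will be electronically extracted from participating practice software systems using an automated data extraction tool".
- **Role in the intervention.** Table 1 makes the same item a key performance measure: "The proportion of patients with CHD with MBS Items 721 or 732 claimed (GP Management Plans or review"). The text above the table gives intervention practices a monthly summary of their performance data. Control practices have no access to the programme.
- **Unrecorded items.** Statistical analyses states that "if not recorded, it will be assumed that the task has not been done".
- **Blinding.** Randomisation accepts that allocation cannot be hidden from practices. It treats outcome collection as in effect concealed because the data arrive by linkage and research staff do not collect them.

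**The concern.** The outcome is a Medicare item, and Medicare data are to be linked, but the source chosen for it is the practices' own software. In this trial four features of that choice combine badly:

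1. The practices that hold the record know their allocation.
2. Only intervention practices are shown their figures on this item each month and asked to improve them.
3. A gap in the record is scored as no plan, so incomplete capture lowers the observed proportion.
4. The stated protection against knowledge of allocation is linkage, and the source assigned to this outcome is not a linked administrative one.

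If the programme makes records more complete, the comparison mixes two effects: more plans delivered, and more of the delivered plans visible. Claims data do not depend on what a practice enters in its clinical record, apart from the claim itself, and the claim is how the protocol defines the outcome. At stake is the interpretation of one secondary outcome.

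**Working it through.** **Plan's own figure.** The only design figure stated is the sample size for the primary outcome, which is not disputed. With 35% v 0.75 × 35% = 26.25%, two-sided 0.05 (sidedness assumed) and 80% power, 435 patients per arm are needed before clustering. The design effect is 1 + (121 − 1) × 0.05 = 7.0, so 435 × 7.0 = 3045 per arm, or 6090 in total, against 6050 stated. This reproduces within 1%.

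**Inputs for the illustration**

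- True plan rate 38% in both arms, so no real effect. The Background gives this figure for Australian patients with CVD, not for this CHD cohort.
- 25 practices per arm, 121 patients per practice and ICC 0.05, from Sample size. That ICC was adopted for the primary outcome; its use here is an assumption.
- Share of delivered plans visible in the software, *s*: assumed. The article gives no value.

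**Formulae**

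- Effective n per arm = 25 × 121 / 7.0 = 3025 / 7.0 = 432.1
- Observed proportion = 0.38 × *s*
- Apparent RR = *s*(intervention) / *s*(control)
- z = difference / √[(p₁(1 − p₁) + p₂(1 − p₂)) / 432.1]
- False-positive rate = P(Z > 1.96 − z) + P(Z < −1.96 − z)

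**Worked case, 95% v 100%.** The observed proportions are 0.361 and 0.380, a difference of 0.019. The standard error is 0.0329, z = 0.58, and the rejection rate is 9%.

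| Capture, control v intervention | Observed proportions | Apparent RR | False positives |
|---|---|---|---|
| equal | equal | 1.00 | 5% |
| 97% v 99% | 0.369 v 0.376 | 1.02 | 5.6% |
| 95% v 100% | 0.361 v 0.380 | 1.05 | 9% |
| 90% v 100% | 0.342 v 0.380 | 1.11 | 21% |
| 80% v 95% | 0.304 v 0.361 | 1.19 | 43% |

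**Sensitivity to the ICC.** For 80% v 95%, an ICC of 0.10 gives a design effect of 13 and 26% false positives. An ICC of 0.20 gives a design effect of 25 and 16%. The apparent RR stays at 1.19; only the chance of declaring it significant falls.

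**What the table shows.** The result depends almost wholly on the assumed capture rates. It runs from negligible to serious within values that the article neither supports nor excludes.

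**The case against.** The strongest reply is that the software may already be reading claims. The outcome carries item numbers, and Table 1 speaks of items claimed. If the extraction tool picks up billed items, more recorded items largely means more claims, which is the outcome itself, and capture should be near complete in both arms. This stands as a limit on size: the 97% v 99% row would then be closer to the truth than the 80% v 95% row. It does not settle the point, because the article does not say how the tool identifies a plan. If billing is what is wanted, the linked claims are the direct source.

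Timing also counts against a large effect. The programme lasts 12 months and the outcome is at 2 years, so a recording gap may have narrowed by then. The article does not show whether it would.

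Three stronger readings are tempting, and the document does not support them:

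- *The result will be materially inflated.* No capture rate is given, so the larger false-positive figures are hypothetical.
- *Plans made at other practices bias the comparison.* They may be missing from a participating practice's software, but nothing indicates that this differs by arm. It is a completeness point, and for a practice-level programme, plans made at the participating practice are a defensible target.
- *The article contradicts itself.* It assigns one source to service use and another to plans. That is a weak choice rather than a contradiction, and a supportive analysis on MBS claims could sit in the analysis plan, which is not shown. The choice of main source, however, is stated in the article.

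It is also fair to say that extraction is automated and the analyst is blinded. Neither removes a difference that arises when the record is made.

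**Conclusion.** The concern holds as a poor choice of source for one secondary outcome. The outcome is defined by Medicare items, the MBS linkage is planned, and the source used instead is held by unblinded practices, fed back in one arm only, and scored so that missing means not done. The concealment argument does not extend to it.

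The size of any bias cannot be derived from the document. Under the assumptions above it ranges from RR 1.02 with about 6% false positives to RR 1.19 with about 43%, the latter falling with a larger ICC. It is probably at the low end if the tool reads billed items. The primary outcome comes from linked admissions data and is unaffected. The change is worth making because it costs little and removes the question, not because a large bias has been shown.

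**What to change.** 1. In Data collection and management, take the plan or review outcome from linked MBS claims for items 721 and 732, over the same window in both arms.
2. Keep the practice-software version as a process measure for feedback or as a sensitivity analysis, and state whether the tool reads billed items.
3. In Randomisation, limit the concealment statement to outcomes obtained from linked sources.

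**Cost.** This is mainly a change of wording, since the MBS linkage is already planned. Two checks come first. Confirm that the MBS extract holds item-level 721 and 732 claims, which the article does not state. Align Study design, which lists hospitalisations, deaths and prescriptions as the administrative data without MBS, with Data collection and management, which includes it.

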### Randomisation

Practices will be randomised 1:1 to intervention (collaborative quality improvement program) or control groups using a computer-generated sequence generated with SAS 9.4 (Proc Surveyselect). Randomisation will be stratified according to two subgroups - rural versus urban location and size of the practice (≤2 versus > 2 GPs in a practice). The statistician performing randomisation will be blinded to practice names and details and only exposed to the practice characteristics that enable stratification. Once allocation is completed, a research team member will be provided the allocation list to enable communication with practices and commence arrangements for their respective requirements. It is not be possible to conceal the group allocation from the practices themselves or the research team delivering the intervention. However, given data is collected via linkage and not performed by research staff, it is essentially concealed. The statistician conducting analysis will be blinded to practice allocation.

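### The statement that data collection is essentially concealed does not hold for blood pressure and smoking, which come from records kept by unblinded practices

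*Protocol article*

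**What the plan says.** All of this is in the protocol article.

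- **Randomisation** concedes that "It is not be possible to conceal the group allocation from the practices themselves or the research team delivering the intervention". It then adds that "given data is collected via linkage and not performed by research staff, it is essentially concealed". The sentence is not restricted to particular outcomes. The section also says that the analysing statistician is blinded.
- **Data collection and management** describes two routes. Admissions, deaths, prescriptions and service use come from administrative sources. By contrast, data on "achieving national risk factor targets (cholesterol, smoking, and BP) will be electronically extracted from participating practice software systems". The same sentence places chronic disease management plans on the practice-software route.
- **Outcomes** makes attainment of national targets for total cholesterol, systolic BP and smoking the fourth secondary outcome, at 2 years. The third is a management plan or review, identified by Medicare items 721 or 732.
- **Intervention and control groups**, Table 1, scores intervention practices on measures that include "Proportion of patients with CHD whose most recent BP reading, taken within the previous 12 months, was less than or equal to 130/80 mmHg" and the proportion recorded as current smokers. The text states that "Intervention practices will receive their summarised performance data monthly". The programme lasts 12 months, and control practices have no access to it.

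**The concern.** Concealment of outcome assessment matters at the point where a value is created. For an admission or a death, that is the hospital or the registry. For BP and smoking status, it is the practice, which knows its arm. If staff repeat a high reading and enter the lower one, or ask about smoking differently, the recorded value moves although the patient has not changed. Only intervention practices have a monthly scorecard that rewards this.

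This is separate from the rule in Statistical analyses that an unrecorded item counts as not done. That rule concerns whether a value is present. The problem here remains even with complete recording in both arms.

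At stake is the reading of one secondary outcome. The protocol as written would allow a difference in BP control or smoking to be presented as resting on concealed data collection.

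**Working it through.** The plan attaches no figure to this point, so there is none to reproduce. The first step sets the text side by side. The second is an illustration on assumed inputs.

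**1. Does the safeguard cover each outcome?**

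| Outcome | Source stated in Data collection and management | Value created by | Concealment statement holds? |
|---|---|---|---|
| Primary: unplanned CVD hospitalisation | State admissions data | Hospital | Yes |
| Secondary 1: major cardiovascular events | Admissions data, National Death Index | Hospital, registry | Yes |
| Secondary 2: medicines | PBS linkage | Administrative record | Yes |
| Secondary 3: plan or review | Practice software, although defined by Medicare items and MBS linkage is also planned | Depends on source used | Unclear |
| Secondary 4: systolic BP, smoking | Practice software | Unblinded practice | No |
| Secondary 4: total cholesterol | Practice software | Laboratory, if it is a laboratory result | More objective |

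Automated extraction prevents research staff from altering a value in transfer. A blinded statistician prevents choices made with knowledge of arm at analysis. Neither affects the reading or smoking answer already in the record. That practice staff enter these values is inferred from the source being practice records; the article does not say who takes each reading.

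**2. Does the incentive coincide with the outcome?**

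Monthly scoring is described for months 0 to 12. Data are collected at baseline, 12 and 24 months, and the outcome is at 24 months. The incentive is therefore active up to the 12-month collection. Scoring is described for no part of the 12 months before the 24-month collection.

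**3. How large could it be? (assumed inputs, none from the protocol)**

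Assume no true effect, a systolic cut-off of 130 mmHg, a usual systolic mean of 130 or 134, a between-patient SD of 15 and a reading-to-reading SD of 5 to 10. If a fraction *f* of high readings is repeated and the lower kept, the proportion at target is

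p(f) = P(first ≤ 130) + f × P(first > 130 and second ≤ 130).

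For mean 134 and reading SD 8, the first term is 40.7% and the second probability is 10.5 points:

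- f = 0.25: 40.7 + 0.25 × 10.5 = 43.3%, ratio 1.06
- f = 0.50: 40.7 + 0.50 × 10.5 = 45.9%, ratio 1.13
- f = 1.00: 40.7 + 10.5 = 51.2%, ratio 1.26

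Over the whole range of assumptions, with no repeats in control practices:

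| Fraction repeated, intervention | Rise in proportion at target | Apparent relative risk |
|---|---|---|
| 25% | 1.7 to 3.2 points | 1.04 to 1.08 |
| 50% | 3.5 to 6.4 points | 1.07 to 1.15 |
| 100% | 7.0 to 12.8 points | 1.14 to 1.30 |

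If control practices also repeat 25% of high readings and intervention practices repeat 50%, the central case becomes 45.9 / 43.3 = 1.06. Only the difference in habit between arms matters. No comparable calculation was made for smoking.

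**The case against.** The strongest reply is that the protocol hides nothing. The sentence just before the safeguard says that practices are unblinded. The safeguard itself says only that research staff do not collect the data, which is true of automated extraction. The Study design section even uses linkage to include practice data. Unblinded routine recording is inherent in a practice-level trial, and the primary outcome is untouched. All of that stands, and it keeps the point modest. But the sentence goes from who transfers the data to the conclusion that allocation is essentially concealed. For values recorded by people who know their allocation, that conclusion does not follow, however linkage is defined.

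Three stronger readings are tempting, and the document does not support them.

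- A reader might infer that monthly scoring biases the 24-month outcome at full strength. Scoring is described only within the 12-month programme, so the table above is not an estimate for month 24.
- A reader might infer that the outcome is a yes/no call on the latest reading against 130/80. That is the Table 1 performance measure. The outcome refers to national targets for systolic BP, with no number and no rule for choosing a reading, which may properly be left to the analysis plan.
- A reader might therefore ask for the mean of all 12-month readings instead of the latest one. That would replace a rule the protocol never sets for the outcome, and averaging cannot recover a high reading that was never entered.

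**Conclusion.** The point holds in limited form. The concealment statement is too broad: it is sound for outcomes from administrative admissions, death and PBS/MBS data, and unsound for BP and smoking in the fourth secondary outcome. The status of the third depends on which source is used. The primary outcome is not affected by this route.

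Recorded BP and smoking can differ by arm without a true change, directly at 12 months and by carry-over at 24. The size cannot be derived from the document. The illustrative relative risks of 1.04 to 1.30 rest on assumed BP distributions and repeat rates, with no repeats in control practices. Repeats there shrink the effect, as does any fading of habits after month 12. The conclusion does not depend on these figures; it follows from the stated data sources and the stated lack of blinding.

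**What to change.** 1. In Randomisation, limit the concealment statement to outcomes taken from administrative admissions, death and PBS/MBS data.
2. State there that BP and smoking come from unblinded practice records, and that differences between arms in them will be interpreted accordingly.
3. State whether items 721/732 for the third secondary outcome are taken from MBS linkage or from practice software, and class that outcome to match.
4. Report mean systolic BP alongside the proportion at target. The mean comes from the same unblinded records, but it helps show whether the distribution moved or mainly the readings near a cut-off.
5. Report cholesterol separately as the more objective component, if it is a laboratory value.

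The cost is a slightly less favourable statement about blinding and a little more reporting. No new data are needed. The bias is disclosed and made easier to judge; it is not removed.
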